#### Secondary

To evaluate the effects of the complex intervention on medication appropriateness after 12 months (T2), as well as on the use of health services, patient quality of life, treatment adherence, and medication safety, as compared with usual care.To study the cost-utility ratio of the intervention as compared with that of usual care.

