## Method/design

### Design

Pragmatic cluster randomized controlled clinical trial with 12 months of follow-up. The unit of randomization is the FP and the unit of analysis is the patient. A cost-utility study will be performed from the perspective of the funder with a time horizon of 1 year.

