#### Secondary outcomes

Use of health services: unplanned and/or avoidable hospitalizations, use of emergency services and PC (FP and nurse).Quality of life: measured using the EuroQol 5D-5L questionnaire [38, 39].Medication safety: measured as the incidence of adverse drug reactions and potentially hazardous interactions, classified using the taxonomy proposed by Otero-López [40].Treatment adherence: measured using the Morisky-Green test [41] and the Haynes-Sackett questionnaire [42].Patient perception of shared decision making: measured using a single, multiple choice question, formulated ad hoc.Cost-utility: time spent on training FPs, cost of teaching staff, time spent on physician-patient interviews, utilities measured using the EuroQol 5D-5L.

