### Explanatory and adjustment variables

#### Patient (first level) variables

Socio-demographics: age, sex, nationality, AC of residence, marital status, socioeconomic status (monthly salary expressed as multiples of the minimum wage), family composition (number of people living at home), housing indicators, social support (Dukes-UNC-11 questionnaire adapted to Spanish [43]), profession, and social class [44].Morbidity: number and description of chronic diseases based on the International Classification of Diseases in PC (ICPC).Pharmacotherapeutic treatment plan: number and type of drugs prescribed, active ingredient, and dose of each drug.

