### Statistical analysis

All analyses will be carried out in accordance with the intention-to-treat principle, with significance set at *p* < 0.05.

Description of baseline characteristics (qualitative and quantitative variables) of patients and professionals for each arm of the study, with corresponding 95% confidence interval (95% CI). Description of patients that abandon the study, including patient characteristics and reasons for loss during follow-up.

Basal comparison between groups using statistical tests for independent samples (Student’s *t* test or chi-square test). Tests for related samples (ANOVA for repeated measures) will be used to analyse changes within groups and between visits.

Analysis of main effectiveness: between-group difference in T1-T0 MAI score, with corresponding 95% CI. Multilevel analysis will be used to adjust models. Difference in MAI score will be considered the dependent variable; baseline patient (first level) and FP (second level) variables and treatment arm will be considered fixed-effect independent variables; and grouping by FP will be considered a random factor. Missing data pertaining to professionals and/or patients will be addressed by replacing missing values with the most recent available or baseline data.

Analysis of secondary effectiveness (non-confirmatory): between-group difference in means or proportions of T2-T0 MAI score will be determined using the appropriate statistical tests and an explanatory model will be adjusted using the same methodology applied to the main outcome variable.

Estimated quality-adjusted life years (QALYs) gained at the population level, with corresponding 95% CI, as determined using parametric methods and bootstrap techniques. Given the 1-year time horizon, no discount rates will be applied.

Calculation of cost-utility ratio: this is an exploratory objective for which a specific design has not been applied. The cost-utility ratio will be estimated by dividing the total cost by the sum of the potential gains expressed in QALYs. A multivariate sensitivity analysis will be performed in which costs will oscillate within the range of uncertainty of a normal distribution. The benefits (QALYs) will also oscillate within the same range.

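### The exploratory cost-utility ratio, as worded, is not incremental in cost or else counts delivery costs only, so it does not give the stated funder-perspective comparison with usual care

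*Protocol article*

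**What the plan says.** Four places in the protocol article bear on this.

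- **Objectives, Secondary** sets a comparative aim: "To study the cost-utility ratio of the intervention as compared with that of usual care".
- **Design** fixes the viewpoint and horizon: "A cost-utility study will be performed from the perspective of the funder with a time horizon of 1 year".
- **Secondary outcomes** names the inputs: "Cost-utility: time spent on training FPs, cost of teaching staff, time spent on physician-patient interviews, utilities measured using the EuroQol 5D-5L". Every cost item in that list is a cost of delivering the intervention.
- **Statistical analysis** gives the formula: "The cost-utility ratio will be estimated by dividing the total cost by the sum of the potential gains expressed in QALYs". The same section labels the objective exploratory. It describes the QALY gain at population level, without writing a contrast between arms.

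Other resource data are planned. Table 1 schedules health-service use and the drug treatment plan at baseline, 6 and 12 months. Service use (admissions, emergency care, physician and nurse contacts) appears as a secondary outcome in its own right. Drug data appear among the adjustment variables: "Pharmacotherapeutic treatment plan: number and type of drugs prescribed, active ingredient, and dose of each drug". Table 1 also has a row headed Costs at 12 months, assigned to the research team, with no content given. Nothing in the article says that the service or drug data are priced or enter the ratio.

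**The concern.** A comparison of two ways of caring for patients asks what each additional QALY costs, so both numerator and denominator must be differences between arms. The stated formula does not say this for cost, and leaves it open for QALYs.

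The cost list raises a second problem. A funder pays for drugs, consultations, emergency care and admissions as well as for training. The intervention is aimed at prescribing, and health-service use is one of its secondary outcomes. If those costs are outside the ratio, a fall in drug spending would not be credited and a rise in admissions would not be charged. What is at stake is whether the reported ratio can inform a choice between the intervention and usual care.

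**Working it through.** The article reports no cost, QALY or cost-utility figure, so there is nothing of its own to reproduce. The check sets the written ratio beside the incremental ratio. **All numerical inputs below are assumptions, per patient, for illustration.**

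**Notation.** D = delivery cost (the listed items). O_int and O_uc = all other care cost in the intervention and usual-care arms. dQ = mean QALY difference between arms. During the trial the usual-care arm is taken to incur none of the listed items.

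**Target:** incremental ratio = (D + O_int - O_uc) / dQ.

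**Reading 1: total cost means all care in the intervention arm.** The written ratio is (D + O_int) / dQ. It exceeds the target by O_uc / dQ, that is, by the whole cost of usual care per QALY gained. The numerator is not incremental.

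**Reading 2: total cost means the listed items.** The written ratio is D / dQ. It differs from the target by (O_int - O_uc) / dQ, and equals it only if other care costs the same in both arms.

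The two readings are alternatives, and their errors should not be added together. Both give the denominator its most favourable meaning, a gain over usual care. If the gain were each arm's own change, there would be no comparator at all.

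**Example under reading 2.** D = 100, drug saving 80 (O_int - O_uc = -80), dQ = 0.010.

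- Listed-cost ratio: 100 / 0.010 = 10,000 per QALY.
- Incremental ratio: (100 - 80) / 0.010 = 2,000 per QALY.

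**Range under reading 2.** D = 150, dQ = 0.01 or 0.02, O_int - O_uc from -300 to +300.

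| O_int - O_uc | dQ | Listed-cost ratio | Incremental ratio |
|---|---|---|---|
| -300 | 0.01 | 15,000 | (150 - 300)/0.01 = -15,000 |
| -300 | 0.02 | 7,500 | (150 - 300)/0.02 = -7,500 |
| 0 | 0.01 | 15,000 | 15,000 |
| 0 | 0.02 | 7,500 | 7,500 |
| +300 | 0.01 | 15,000 | (150 + 300)/0.01 = 45,000 |
| +300 | 0.02 | 7,500 | (150 + 300)/0.02 = 22,500 |

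With dQ positive, a negative incremental ratio means lower cost with more QALYs. The listed-cost ratio is the same in every row with the same dQ. It cannot separate an intervention that saves money from one that costs three times as much per QALY as the ratio shows (45,000 against 15,000).

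**The case against.** The best defence has four parts.

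- **The analysis is exploratory.** This stands. The article says that no specific design was applied for it, and the primary MAI analysis and sample size do not depend on it. That limits severity, but does not reconcile the formula with the objective.
- **For the listed items the numerator is already a difference.** This also stands. Control physicians receive the training only after the intervention is over (Discussion), so usual care bears essentially none of those costs during the trial. Delivery cost over the QALY gain from usual care is then an incremental ratio for delivery cost. The defence does not extend to drugs and services.
- **The article may condense a fuller costing plan.** The Costs row in Table 1 is unspecified, the cost list is not called exhaustive, and total cost is unrestricted in the formula. Drug and service costs may therefore be intended, and it would be too firm to say they are definitely excluded. But including them moves the plan to the all-care reading, where the formula lacks the subtraction of usual-care cost.
- **Gains can be read as gains over usual care.** This is reasonable and is granted in the calculation above. A reader might instead infer that total cost is divided by total QALYs. The article says gains, so that reading is not supported.

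A reader might also take the sensitivity-analysis sentence, "The benefits (QALYs) will also oscillate within the same range", as varying QALYs on the scale of costs. It follows a reference to the uncertainty range of a normal distribution and more plausibly means the same kind of range. Silence there on cost-QALY correlation and clustering is detail that an article may leave to the analysis plan. Neither is counted as an error.

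**Conclusion.** The point holds for two matters only: the definition of the ratio and the scope of its costs. As worded, neither reading of total cost delivers the comparison with usual care from the funder's perspective. All care gives a numerator that is not incremental; the listed items give a ratio blind to drug and service costs.

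The size cannot be estimated from the article. Under the assumed inputs, the listed-cost ratio stays between 7,500 and 15,000 while the incremental ratio runs from -15,000 to 45,000. These figures show direction and possible scale, and predict nothing about this trial. The two ratios agree if other care costs the same in both arms.

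A reader might infer that the trial cannot support a cost-utility comparison. The documents do not support that: utilities, service use and drug plans are scheduled at all three visits, so the weakness lies in the stated ratio and not in the planned data. Severity is modest, because the objective is exploratory and the primary analysis is untouched.

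**What to change.** 1. Define the ratio as (mean cost intervention - mean cost usual care) / (mean QALY intervention - mean QALY usual care).
2. Include drug, primary care, emergency and hospital costs by attaching unit costs to the data already collected, and add delivery cost. Otherwise, state that the ratio covers delivery cost only and is not a full funder-perspective result.
3. Say what the Costs row in Table 1 contains, so that it agrees with the list under Secondary outcomes.
4. Obtain the uncertainty by a bootstrap that resamples physicians, the unit of randomization, and keeps each patient's cost and QALY together.

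The cost is a change of wording in the protocol and analysis plan, plus the work of attaching unit costs; no new patient data are needed. The resulting ratio may be less favourable than one based on delivery cost alone, so the definition is best settled before results are known.

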## Discussion

This pragmatic clinical trial will involve the participation of FPs from over 50 PC health centres in different geographic areas of Spain, thus ensuring a high level of external validity, given that the PC model implemented throughout the country is relatively homogeneous.

To address the potential contamination among patients of the same cluster, the FP is considered the unit of randomization and the patient the unit of analysis. Still, there is evidence of contamination when healthcare professionals working in the same teams are randomized. To palliate this problem, the following measures will be introduced. First, during the welcome and training session with all participating FPs, we will avoid sharing too many details regarding the complex intervention [45]. Second, participating FPs will be asked to sign a confidentiality agreement once they are randomly assigned to the intervention or control group. Third, the intervention group will be periodically reminded about the importance of avoiding the exchange of any information with other participating FPs during the intervention. Last, by signing the researcher’s commitment, those FP eventually belonging to the control group agree to receive the same training activity once the intervention is over.

Due to the nature of the intervention, it cannot be masked. However, outcome evaluation will be conducted by skilled FPs and pharmacists that are blinded for treatment allocation. The statistician conducting the analysis will neither know to which study arm a given patient has been assigned.

The variability in clinical practice of the different physicians involved and their baseline knowledge on the content covered in the intervention could result in lower than expected differences between groups after completion of the intervention. To address this potential bias, variables related to FPs’ prior training in polypharmacy, multimorbidity, and/or shared decision making will be collected and adjusted for in the multilevel model. Furthermore, the MOOC format of the training material will ensure homogenization of the training received by the FPs. Video technology and online courses have shown to be powerful tools to empower both patients and health professionals and have the potential to significantly improve the delivery of care in an increasingly complex healthcare system [46].

FPs who agree to participate in an experimental study are potentially more interested in the subject, just as patients who agree to participate may share certain common features in terms of health-related awareness and motivation, which can lead to bias. Although better results than those obtained including less selective participants may occur, this phenomenon would have a conservative effect (i.e. it would decrease the magnitude of the difference between the two groups). Moreover, participating FPs could modify or improve their prescribing habits just as a response to their awareness of being observed (Hawthorne effect). This may dilute differences between intervention and control groups regarding the appropriateness of prescription.

Although the analysis of the effect of the intervention on quality of life is non-confirmatory and the expected changes are limited over a short period of time, we consider it essential to include this outcome in the study. Firstly, between-group differences may be detected despite not being highly significant, and secondly, measurement of quality of life changes allows the incorporation of outcome variables reported by patients themselves, and facilitates the calculation of utilities for the cost-utility analysis. This will enable responding to some of the shortcomings and limitations of previous interventions as detected by Patterson et al. [25].

It is essential to provide evidence concerning interventions on PC patients with polypharmacy and multimorbidity, conducted in the context of routine clinical practice, and involving young-old patients with significant potential for preventing negative health outcomes.

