### Intervention

#### Intervention group

A complex intervention with two phases is conducted:First phase: FP training. This will consist of a previously designed training activity, delivered using the massive online open courses (MOOC) format, including basic concepts relating to multimorbidity, appropriateness of prescribing, treatment adherence, the Ariadne principles, and physician-patient shared decision making.Second phase: Physician-patient interview based on the Ariadne principles.

This intervention has been developed in accordance with the recommendations and taxonomy proposed by the Cochrane Effective Practice and Organisation of Care Review Group (EPOC). The intervention is described in detail in Fig. 2, following the approach proposed by Perera et al. [36].

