### Variables

FPs will provide their data before the start of the study. Patient data will be collected by the recruiting FP, who will also be responsible for patient follow-up. All information will be recorded in a case report form designed for the study. Each FP will access the form from his/her personal computer via the project website using a personal identification code. Three visits are defined for patient data collection: baseline (T0), 6 months (T1), and 12 months (T2) (see Table 1).

**Table 1 Tab1:** Visit plan

	T0 (baseline)		T1 (6 months)	T2 (12 months)	Responsible entity
Confirm inclusion/exclusion criteria	X				FP
Written informed consent	X				FP
Socio-demographic variables	X				FP
Morbidity variables and drug treatment plan	X		X	X	FP
Randomization of FPs		X			RU
FP intervention (intervention group)		X			RT
Patient intervention (intervention group)		X	X		FP
Use of health services	X		X	X	RT
Medication adherence	X		X	X	FP
Medication safety			X	X	FP
Quality of life	X		X	X	FP
Costs				X	RT
MAI	X		X	X	EE EC

*FP* family physician, *RU* research unit, *RT* research team, *EE* external evaluator, *EC* evaluation committee, *MAI* medication appropriateness index

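### Control FPs may take the training course once the intervention ends, a point not tied to T2, so the secondary 12-month and 1-year comparisons could be diluted

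*Protocol article*

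**What the plan says.** The Discussion lists four measures against contamination between FPs. The last is that "those FP eventually belonging to the control group agree to receive the same training activity once the intervention is over". The text does not define when that point is reached.

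The timing has to be read from elsewhere:

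- **Variables, Table 1 (visit plan).** The row for FP training, "FP intervention (intervention group"), is marked only in the column between T0 and T1. The row "Patient intervention (intervention group") is marked in that column and at T1. Neither is marked at T2. No row shows training of control FPs at any time.
- **Intervention group.** The course is the first of two phases, "including basic concepts relating to multimorbidity, appropriateness of prescribing, treatment adherence, the Ariadne principles, and physician-patient shared decision making". The second phase is the Ariadne-based interview with the patient.
- **Design.** "Pragmatic cluster randomized controlled clinical trial with 12 months of follow-up", with a cost-utility study over one year.
- **Objectives, Secondary.** "To evaluate the effects of the complex intervention on medication appropriateness after 12 months (T2"), together with service use, quality of life, adherence and safety, all against usual care.
- **Statistical analysis.** The T2 analysis is the "between-group difference in means or proportions of T2-T0 MAI score". It is labelled non-confirmatory, and cost-utility is labelled exploratory.

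**The concern.** A deferred offer of training is a sensible way to keep control FPs engaged, but it protects the comparison only if it is deferred past the last outcome. Here it is tied to the end of the intervention, and the visit plan shows no intervention activity after month 6, while outcomes run to month 12.

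The course covers appropriateness of prescribing, which is what the MAI measures. The Discussion itself expects FPs' existing knowledge of the course content to shrink the between-group difference. A control FP who took the course at month 7 would bring some of that knowledge to patients still in follow-up. The T2 contrasts would then be biased toward no difference. Training time and teaching cost, which the protocol counts as cost inputs, would also arise in the control arm within the 1-year horizon. Analysis by intention to treat keeps patients in their allocated arm but does not restore a usual-care comparator.

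**Working it through.** **1. Timing, from the protocol's own schedule**

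| Item | Last mark or end point | Source |
|---|---|---|
| FP training, intervention arm | between T0 and T1 | Table 1 |
| Patient intervention | T1 (6 months) | Table 1 |
| Primary contrast | T1-T0 | Statistical analysis |
| MAI, service use, adherence, safety, quality of life | T2 (12 months) | Table 1 |
| Costs | T2 only | Table 1 |
| Cost-utility horizon | 1 year | Design |

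Window left open: 12 − 6 = 6 months, which is 6/12, or half, of the cost-utility horizon. The primary contrast lies before this window.

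Two details in the Discussion suggest that the end of the intervention is not simply the end of the study. It speaks of group differences observed once the intervention has been completed, and it limits the reminders to intervention FPs to the intervention period. Neither settles the date.

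**2. The plan's sample size**

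Inputs from Sample size: difference 2, SD 6, power 80%, 5 patients per FP, ICC 0.03, losses 20%. Alpha is 0.05 (Statistical analysis); two-sided is my assumption.

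- Normal approximation: n per arm = 2 × (1.96 + 0.842)² × 6² / 2² ≈ 141.3, so 142. The t-based solution is 142.2, so 143 per arm and 286 in total, as stated. (One-sided would give 112 per arm, which does not match.)
- DE = 1 + (5 − 1) × 0.03 = 1.12; 286 × 1.12 = 320.3, stated as 320.
- 320 / (1 − 0.20) = 400, as stated. Evaluable per arm: 200 × 0.80 = 160.

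The stated figures reproduce.

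**3. Illustration of dilution at T2**

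Two assumptions are not in the protocol: that the 6-month difference and SD also hold at T2, and that controls gain a share f of the effect before T2.

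- SE = 6 × √(2 × 1.12 / 160) = 0.710
- Contrast at T2 = 2 × (1 − f)
- Power ≈ Φ(contrast / SE − 1.96)

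| Assumed f | T2 contrast | contrast / SE | Power |
|---|---|---|---|
| 0 | 2.0 | 2.82 | 0.804 |
| 0.25 | 1.5 | 2.11 | 0.561 |
| 0.50 | 1.0 | 1.41 | 0.291 |
| 0.75 | 0.5 | 0.70 | 0.105 |

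**The case against.** The strongest reply is that the phrase is merely undefined. It names neither T1 nor any date, and it appears in a list of safeguards against contamination, where training controls in mid-follow-up would defeat the purpose. Reading it as the end of the study fits the 12-month follow-up, the usual-care comparison and the absence of a control-training row in Table 1. The patient intervention is still marked at T1, so it need not be finished there. Fig. 2, which describes the intervention in detail, and the signed commitment are not available to settle the matter.

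Much of this stands. A reader might infer that control training is scheduled at six months; the protocol does not say so. A reader might also infer that the T2 analysis would compare two trained arms with no contrast left. That is not supported either, because controls are promised only the course, while the structured interview remains specific to the intervention arm. Nor does the protocol claim any power at T2, so the power figures show no actual loss against a stated target.

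What does not stand is that this is detail an article may leave out. The article states a timing rule to which FPs commit. Followed as written and read with Table 1, that rule allows training during follow-up, and nothing in the text defers it past T2.

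**Conclusion.** The point holds as a risk that the wording leaves open, not as a demonstrated flaw in the trial's conduct. The rule permits control FPs to be trained in the roughly six months between T1 and T2. If they were, the 12-month comparisons of MAI, service use, quality of life, adherence and safety, and months 6 to 12 of the cost-utility comparison, would be diluted toward no difference. They would not be abolished.

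The consequence is limited. The primary T1-T0 analysis is unaffected provided that training follows the T1 assessment, and the first six months of the cost-utility comparison are likewise clean. The comparisons at risk are secondary or exploratory.

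The size cannot be derived from the protocol. The 56% and 29% figures depend wholly on the assumed shares and on planning values given only for six months. The change is still worth making: it is cheap, and the bias would be hard to correct afterwards.

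**What to change.** In the Discussion, replace the undefined end point of the control-training sentence with a fixed one: control FPs receive the course only after T2 data have been collected for all patients in the trial. Use the same wording in the researcher's commitment. The cost is one sentence in each document and a wait of about six months longer for control FPs, compared with training straight after T1.

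If earlier training cannot be avoided, record the date on which each control FP takes it, count its cost in the control arm, and describe the T2 and 1-year results as early versus delayed training and not as intervention versus usual care.
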